## Abstract

**Background:**

Freezing of gait (FoG) is one of the most disabling symptoms of Parkinson disease (PD). Detecting and monitoring episodes of FoG are important in the medical follow-up of patients to assess disease progression and functional impact and to adjust treatment accordingly. Although several questionnaires exist, they lack objectivity. Using wearable sensors such as inertial measurement units (IMUs) to detect FoG episodes offers greater objectivity and accuracy. There is no consensus on the number and location of IMU, type of algorithm, and method of triggering and scoring the FoG episodes.

**Objective:**

The objective of this study is to investigate the use of multiple wearable sensors sets to detect FoG in patients with PD during various walking tasks under different medication conditions.

**Methods:**

This single-center, prospective cohort study (DetectFoG) will include 18 patients with PD. Patients will be fitted with 7 IMUs and will walk a freezing-provoking path under different tasks—“single task,” “dual motor task,” or “dual cognitive task”—and medical conditions corresponding to levodopa medication (“on” or “off”). Passages will be videotaped, and 2 movement disorder specialists will identify FoG episodes in the videos. The accuracy, sensitivity, specificity, positive predictive value, and negative predictive value of the most effective combination of wearable sensors for detecting FoG episodes will be studied.

**Results:**

The study is currently in the data collection phase, having commenced recruitment in February 2024. Once all data have been gathered, the data analysis will commence. As of August 2024, 3 patients have been recruited. It is anticipated that the results will be published by the end of 2025.

**Conclusions:**

Detecting FoG episodes in various medical and clinical settings would provide a more comprehensive understanding of this phenomenon. Furthermore, it would enable reliable and objective monitoring of the progression of this symptom based on treatments and the natural course of the disease. This could serve as an objective tool for monitoring patients and assessing the severity and frequency of FoG.

**Trial Registration:**

Clinicaltrials.gov NCT05822258; https://www.clinicaltrials.gov/study/NCT05822258

**International Registered Report Identifier (IRRID):**

DERR1-10.2196/58612

## Introduction

Affecting more than 8.5 million people worldwide in 2019, Parkinson disease (PD) is the second most common neurodegenerative disease [1]. PD is diagnosed using criteria from the UK Parkinson’s Disease Society Brain Bank [2] and is defined by the cardinal symptoms of tremor, bradykinesia, rigidity, and postural instability, along with other motor and nonmotor symptoms [3].

Among the various motor symptoms, freezing of gait (FoG), defined as a “brief and episodic absence or marked reduction in the forward progression of the feet despite the intention to walk” [4], is one of the most disabling symptoms of PD. In advanced and severe forms of PD, FoG occurs in 50% to 80% of cases [5]. FoG is correlated with PD severity and disease duration [6]. It increases the risk of falls [7] and loss of independence and affects patients’ quality of life [8].

The detection of FoG episodes is an important issue for patient follow-up and treatment adjustment. Various subjective and objective methods can be used to assess these symptoms. Daily completion of a motor diary by the patient is one possibility for assessing these symptoms, but it relies on the patient’s subjective judgment and is often discontinued after a few days or is not feasible in the presence of cognitive impairment [9]. Objective scores with predefined exercises (eg, double spot walking, 180° turning, etc) are available to assess FoG episodes during medical consultations; however, these exercises do not always trigger FoG episodes due to several reasons. First, the phenomenon known as the “white coat effect,” whereby patients may perform differently in the presence of medical professionals, can alter their natural response and reduce the likelihood of FoG episodes [10]. Second, the structured nature of clinical assessments often causes a switch from automatic to goal-directed pathways, reducing the occurrence of FoG episodes, which typically occurs in more automatic walking scenarios [11]. Finally, the predefined exercises are constrained by time, unfamiliarity, and the artificiality of the clinical environment, which can influence patients’ natural gait patterns. Thus, they fail to provide accurate information on the frequency and severity of FoG episodes in daily life [11]. One potential alternative method involves videotaping patients in different contexts and conducting a postscored examination, considered the gold standard, although this approach demands time and expertise [11].

To overcome these limitations, wearable sensors, such as electromyographs, electroencephalography electrodes, or inertial measurement units (IMUs), provide a solution for automatic FoG detection. The combination of accelerometer and gyroscopes data from an IMU seems to be the most widely used solution with high performance (sensitivity: 86%; specificity: 92.9% [12]). This compact sensor is easy to install and allows FoG assessment both in clinical practice and during daily living [9,13].

Despite numerous studies and literature reviews on the use of these wearable sensors for FoG detection, there is as yet no consensus in the literature on the optimal methodology for their use. It is likely that this discrepancy stems from the inherent variability in the protocols used. Indeed, there is considerable heterogeneity in the protocols for triggering [11] (medical condition: “on” or “off” levodopa treatment; freezing-provoking path; and dual-task conditions). In fact, there are few studies that directly compare FoG episodes in “on” and “off” conditions with small cohorts and a low number of participants [11,12,14]. Furthermore, many locations including feet, shin or ankle, thigh, and pelvis have been investigated [15]. The use of multiple sensors provides a more detailed and holistic view of the patient’s movements, enabling the capture of subtle changes that may not be detectable with a single sensor [15]. An IMU is cost-effective and straightforward to wear, rendering it suitable for both laboratory evaluation and daily use. Even if patients prefer to wear sensors solely at the wrist, such as a stopwatch, or conceal them beneath clothing at the ankle or on a belt (lower back), as demonstrated by O’Day et al [15], the placement of sensors on multiple body parts could enhance the robustness of FoG detection across various walking tasks and different FoG subtypes. Furthermore, examining FoG under dual-task conditions provides a more comprehensive understanding of how cognitive load impacts freezing episodes, which only a few studies have addressed [16-20]. Finally, several other variables may confound the study, including the wide age range of cohorts (aged 7-118 years) and the diverse range of FoG episodes (50-1110) [21-23]. Therefore, this study is innovative as it stands out for its ability to replicate findings across various conditions, particularly the medical condition. Furthermore, it explores the effects of dual-task scenarios and optimal sensor placement in a larger cohort than those found in the literature, significantly enhancing our understanding of the underlying mechanisms. These multiple dimensions provide a more nuanced and robust perspective, allowing for better generalization of the results and improving practical applications in medical settings.

Regardless of the wearable sensors used or the freezing protocol, the accuracy of detection is sensitive to the type of algorithm [9,11,12,23]. Yet, the algorithms used to detect FoG episodes are controversial, especially for real-time detection. The threshold method provides a straightforward approach to the implementation and interpretation of algorithms. In this context, the freezing index—defined as the ratio between the power bands of freezing (3-8 Hz) and locomotion (0.5-3 Hz)—is the most commonly used feature in threshold-based algorithms [9,11,12,23]. This single feature accurately detects many FoG episodes (sensitivity: 84.3%; specificity: 78.4% [24]), but detection fails when no motion is observed and voluntary stops may be mistakenly classified as FoG [17]. Adding multiple indices can enhance algorithm performance, but it also increases complexity and the difficulty of tuning thresholds [25,26]. To address these limitations, machine learning (ML) algorithms have been developed to improve FoG detection performance. Indeed, ML algorithms could better fit the model to increase the accuracy of the models; this is a subfield of artificial intelligence that gives an algorithm the ability to learn without being explicitly programmed [12]. Among the various ML algorithms, support vector machine, multilayer perceptron, and ensemble classifiers (eg, random forest or AdaBoost) have proven to be the most efficient. Determining the best ML algorithm is challenging due to the highly heterogeneous nature of the training data. A limitation of ML algorithms is that training the model and processing the data can require high computational cost. Fortunately, advances in computer technology now offer the possibility of early or real-time detection with ML models [12].

The primary objective is to assess the accuracy of the optimal combination of wearable sensors for detecting FoG episodes in patients with PD. The secondary objectives of this study include measuring the specificity, sensitivity, positive predictive value (PPV), and negative predictive value (NPV) of the optimal combination of wearable sensors for detecting FoG episodes. Regarding the setup, we also aim to compare its performance (accuracy, sensitivity, specificity, PPV, and NPV) across various clinical and medical conditions.

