##### Video Recording and Window Labeling

During each visit, and during trials designed to induce freezing episodes, patients will be recorded using 14 synchronized Miqus M3 cameras (Qualisys). These cameras will record at a resolution of 1824 × 1088 pixels with a frequency of 25 Hz. FoG episodes will be identified from the videos by 2 movement disorders specialists ([name]) independently using QTM 2020 software (Qualisys). The start of a freezing episode is defined as “the moment when the stepping foot does not leave the ground despite a clear intention to step,” and the end is defined as “the moment when the stepping foot begins or resumes an effective step” [32]. In cases where there is disagreement about the presence of a FoG episode, the specialists will discuss and reach a consensus. Following the methodology of Pardoel et al [32], the data timeline will be segmented into 2-second windows with a 0.4-second shift between windows (80% overlap). Windows will be labeled as “FoG window” when the entire window corresponds to a period of FoG. Windows not meeting this criterion, either during periods without FoG or during transitions between FoG episodes and non-FoG periods, will be labeled as “no-FoG window.” The relative duration of FoG will be assessed by calculating the ratio of FoG windows to the total number of windows. This ratio provides a measure of the freezing time while accounting for the window labeling method used. To ensure comparability with other studies and to mitigate the effect of varying labeling methods across research [32,38], we will also calculate the total number of FoG episodes and the cumulative freezing time based on onset and end events, categorized by task type, session, and patient. This approach will facilitate meaningful comparisons with existing literature on FoG detection methodologies.

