#### Primary Outcome

The main objective of our study is to identify the most relevant features and locations of wearable sensors for detecting FoG episodes. The Relief-F technique will rank features extracted from data collected by all sensor segments. The top-ranked features across all subjects will indicate the most critical sensors for detecting FoG episodes, and these features will be used in model training and validation. The LOSO method will be used for validation, and accuracy will be computed for each subject. Furthermore, Relief-F analysis will be conducted individually for each subject to potentially reveal redundancy in the top-ranked features across subjects. Feature extraction, selection, model training, and validation will be implemented using Python 3.0 (PythonLabs) scripts.

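### Raw window-level accuracy as the primary figure depends on how many windows are FoG and has no never-FoG reference, so a high value does not by itself show detection

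*Protocol article*

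**What the plan says.** The Introduction names accuracy as the primary measure: "The primary objective is to assess the accuracy of the optimal combination of wearable sensors for detecting FoG episodes in patients with PD". Sensitivity, specificity, PPV and NPV are secondary. Under Primary Outcome the article adds: "The LOSO method will be used for validation, and accuracy will be computed for each subject". Model Training counts true and false positives and negatives window by window.

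Video Recording and Window Labeling divides the recording into "2-second windows with a 0.4-second shift between windows (80% overlap"). A window is positive only "when the entire window corresponds to a period of FoG"; every other window, including transitions, is negative. The same section plans a measure of freezing time by "calculating the ratio of FoG windows to the total number of windows", which is p.

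On conditions, the Introduction says: "we also aim to compare its performance (accuracy, sensitivity, specificity, PPV, and NPV) across various clinical and medical conditions". Secondary Outcomes puts accuracy, sensitivity and specificity, but not PPV or NPV, into a mixed-effects model.

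The article mentions neither a balanced or chance-corrected version of accuracy nor a reference value for a model that never calls FoG.

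**The concern.** Accuracy is an average of sensitivity and specificity weighted by the class shares. When few windows are FoG, specificity carries nearly all the weight, and a model that labels everything no-FoG scores close to 100%. The study's purpose is to show that a sensor set detects FoG, and a primary figure that can be high without any detection does not answer that question alone.

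A second consequence follows for the comparisons across task and medication state. Accuracy, PPV and NPV can differ between conditions only because patients freeze more in one of them, even if the detector behaves identically in both.

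**Working it through.** The article gives no target accuracy and no value of p, so there is no planned figure to reproduce. The equations in Model Training are a figure not shown in the copy reviewed; the usual definition, correct windows over all windows, is used here.

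**Inputs**
- Detector A: "sensitivity: 86%; specificity: 92.9% [12"], cited in the Introduction for IMU data.
- Detector B: sensitivity 84.3% and specificity 78.4%, cited in the Introduction for the freezing index.
- Both pairs are literature values for other algorithms. Using them as window-level values here is an illustration.
- p is assumed.

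**Step 1: why p can be low.** An episode of d seconds keeps roughly (d − 2)/d of its freezing time as FoG windows, and none if d is below 2.
- At d = 3, the share kept is 1/3 = 33%; at d = 5, it is 3/5 = 60%.
- Model Validation requires only one episode per patient, and the Protocol section expects some patients to have few or none in a block.
- Assume one 5-second episode, which gives about (5 − 2)/0.4 = 7.5 FoG windows, and trials of 30 to 60 seconds.
- Six trials of 30 s: total 6 × 28/0.4 = 420 windows, so p = 7.5/420 = 1.8%.
- 36 trials of 60 s (18 at each of two visits, assumed): total 36 × 58/0.4 = 5,220 windows, so p = 7.5/5,220 = 0.14%.
- Never-FoG accuracy for that patient is therefore 98.2% to 99.9%. If all of a patient's episodes last under 2 s, p = 0 and it is 100%.

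**Step 2: break-even.** Never-FoG accuracy is 1 − p. It exceeds Se × p + Sp × (1 − p) when p < (1 − Sp)/(1 − Sp + Se).
- A: 0.071/(0.071 + 0.86) = 0.0763, or 7.6%.
- B: 0.216/(0.216 + 0.843) = 0.204, or 20.4%.

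| p | Never-FoG | A | B |
|---|---|---|---|
| 2% | 98.0% | 92.8% | 78.5% |
| 5% | 95.0% | 92.6% | 78.7% |
| 10% | 90.0% | 92.2% | 79.0% |
| 20% | 80.0% | 91.5% | 79.6% |
| 30% | 70.0% | 90.8% | 80.2% |

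**Step 3: conditions.** With Se and Sp unchanged, the accuracy difference is (Se − Sp) × (change in p). For p from 2% to 20%:
- A: (0.86 − 0.929) × 0.18 = −1.2 points.
- B: (0.843 − 0.784) × 0.18 = +1.1 points.
- A low-sensitivity model (Se 0.50, Sp 0.97, assumed): −0.47 × 0.18 = −8.5 points.
- PPV for A at p = 2%: 0.0172/(0.0172 + 0.0696) = 20%.
- PPV for A at p = 20%: 0.172/(0.172 + 0.0568) = 75%.

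**Step 4: balanced accuracy, (Se + Sp)/2.** A gives 0.895 and B gives 0.814 at every p; never-FoG gives 0.50. The condition difference is zero when Se and Sp do not change.

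**The case against.** Four points stand against a stronger reading.

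- **Low p is not established for the study as a whole.** The provoking path, the dual tasks, the off-levodopa visit, recruitment of self-reported freezers and exclusion of patients without FoG all push p up. Above 7.6% (A) or 20.4% (B) the never-FoG model loses. This limits the claim to subjects or conditions with few FoG windows, which the article's own rules allow.
- **A reader might infer that accuracy will choose the wrong sensors or a non-detecting tree.** The text does not support that. Primary Outcome has Relief-F rank the features and so point to the sensors. Model Training evaluates the tree variants on all five measures and states no rule for choosing among them. Remarks elsewhere about optimizing or maximizing accuracy are general.
- **A reader might also infer that the results by condition are an artefact of prevalence.** That goes too far. Sensitivity and specificity do not depend directly on p and are already in the mixed-effects model. At the cited values the shift in accuracy is about 1 point, and its sign depends on which of Se and Sp is larger. PPV moves much more, but it is in the stated aim and not in that model.
- **The planned secondary results would expose a never-FoG model**, since its sensitivity is 0%. This is true, but it does not repair the primary figure. It confirms that the primary figure needs other measures beside it before it can be read.

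**Conclusion.** The point holds in a limited form. Raw accuracy per left-out subject depends on the share of FoG windows and is planned without a never-FoG reference, so a high value is not evidence of detection on its own. At the cited performance values, the range of p in which a never-FoG model scores higher is below 7.6% or below 20.4%. The first range rests on Se 86% and Sp 92.9%, the second on 84.3% and 78.4%. Whether a given subject falls in that range is not known from the article. It is likely for patients with few or short episodes and unproven for the cohort average.

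For the comparisons across conditions, dependence on p is a small matter for accuracy unless sensitivity is far from specificity, and a large one for PPV. The correction should be made before the analysis begins; the article says this waits until all data are gathered.

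**What to change.** - Make balanced accuracy, (Se + Sp)/2 over held-out subjects, the primary figure, and name it as the criterion for any choice among the tree variants.
- Sensitivity is undefined for a held-out subject with no FoG window, so state the rule in advance. Take sensitivity over subjects with at least one FoG window, or from the pooled held-out windows, and specificity over all subjects. Report how many subjects have no FoG window.
- Report raw accuracy for each subject beside that subject's never-FoG accuracy, 1 − p. The FoG window ratio already planned supplies p.
- Base the comparisons across task and medication state on sensitivity and specificity. Give accuracy, PPV and NPV by condition descriptively, with p shown.

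The cost is a change of wording, a few lines of code and the extra rule for subjects without FoG windows. Sensitivity will be imprecise for subjects with only a few FoG windows. Raw accuracy remains available for comparison with other studies. The headline figure may look less favourable.

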## Methods

### Study Design and Participants

This study is a single-center, prospective cohort trial (DetectFoG) involving patients with PD with FoG at the University Hospital of Rennes. Patients will be recruited from the neurology department of University Hospital of Rennes during their visit to the neurologist. This study aims to include a total of 18 patients. To mitigate potential issues such as withdrawal of consent, absence of FoG during neurologist annotation, loss of follow-up (failure to attend the second visit), or inability to complete the required number of passages (fewer than 6), initially, 20 patients will be enrolled. Participants experiencing any of these issues will be excluded from the study.

Inclusion criteria will include patients older than 18 years diagnosed with PD according to the UK Brain Bank criteria. Patients must self-report as freezers, scoring between 1 and 3 on question 13 of the Movement Disorder Society-Unified Parkinson’s Disease Rating Scale (MDS-UPDRS) II [27], and be capable of walking 30 m without assistance to complete the freezing-provoking path. Exclusion criteria will apply to patients scoring less than 20 out of 30 on the Montreal Cognitive Assessment [28] who are unable to give informed consent and those with neurological, orthopedic, or rheumatic comorbidities that could impact gait and ability.

### Ethical Considerations

The study design was approved by the ethical committee of Ile de France III (23.01067.000298-MS01) on October 1, 2023. All data collection will adhere to applicable guidelines and regulations. Participants will provide informed consent before enrolling in the study.

### Protocol

After verifying the inclusion and exclusion criteria, the neurologist will notify the principal investigator (KJ). The principal investigator will then contact the patients to provide comprehensive and understandable information about the study’s objectives, as well as their right to refuse participation or withdraw at any time. If the patients consent and sign the consent form, they will participate in 2 visits separated by 2 weeks (±7 days), encompassing both “on” and “off” phases of levodopa treatment (Figure 1).

**Figure 1 figure1:**
[figure not shown]
Timeline of study. IMU: inertial measurement unit.

For organizational purposes, the first visit (inclusion visit) will occur during the “on” phase of levodopa medication, while the second visit (follow-up visit) will be during the “off” phase. During the “on” phase, patients will be assessed when oral treatment maximally improves dopa-sensitive PD symptoms (best “on” state, typically 1-2 hours after ingestion). This state will be determined based on patients’ subjective assessment, similar to their daily motor self-assessments (home diaries), which has been established as reliable in various studies [29-31]. Assessment during the “off” phase will occur after 12 hours without treatment, preferably in the morning before the first levodopa dose.

During each visit, participants will walk on a freezing-provoking path at a comfortable speed under 3 different clinical conditions (single task [ST], dual cognitive task [DCT], and dual motor task [DMT]). The Pardoel freezing-provoking path, known to induce FoG episodes [32], includes standing up, walking with a slalom (left and right turns), navigating a narrow passage with a 180° turn, and returning straight, with 2 designated stops—one chosen by the patient and another in front of a chair (Figure 2).

